## Abstract

**Background:**

Anorexia nervosa (AN) is a life-threatening disease with a low effectiveness of treatment. The high relapse and mortality rate indicate new treatment approaches are needed. Here, we represent the protocol for randomized clinical trial (RCT) of transcranial direct current stimulation (tDCS) efficiency in the AN treatment. The main purpose of the 3-week RCT is to determine the effect of tDCS on the mental state and advances in nutritional rehabilitation in patients with AN.

**Methods:**

50 female inpatients (13-25 years old, body mass index (BMI) 17.5 kg/m2 or less) will be randomly allocated into groups: active (n=25) and sham (n=25) tDCS. Thirty 25-minute tDCS sessions (applied current at 2mA) will be given to DLPFC (F3 anode/F4 cathode) twice a day for 3 weeks on working days parallel to treatment as usual. The primary outcome measures include changes in symptoms related to eating disorders, as assessed by the Eating Attitudes Test (EAT-26), following tDCS sessions over a 3-week trial period. The secondary outcome measures include changes in: brain bioelectric activity, anthropometric measurements, mood, nutritional status, neurocognition, psychological symptoms, selected biological markers related to stress, food intake, inflammation and neurotrophins.

**Discussion:**

This paper describes the evaluation of a 3-week tDCS-based intervention for AN patients. The study design was developed by a multidisciplinary research team to assess the treatment effect, taking into account various types of variables. This approach could help in better understanding the potential therapeutic tDCS strategy in AN.

**Clinical trial registration:**

www.ClinicalTrials.gov, identifier NCT05814458.

## Introduction

### Background and rationale

Anorexia nervosa (AN), a form of eating disorder, is identifiable through several characteristic symptoms. These encompass the adoption of a restrictive diet leading to weight loss, a distorted perception of one’s body, the fear of gaining weight, decreased libido, multidimensional cognitive dysfunction, and the implementation of hedging and avoidance strategies (1). AN, recognized as a life-threatening condition, transcends global boundaries, affecting individuals across diverse socio-economic strata. Its prevalence is reported to be between 0.3-0.6% in women and 0.1% in men (2). The intricate nature of AN treatment is marked by numerous complications, resulting in a significant number of deaths. Particularly alarming is the mortality rate among girls and women aged 15 to 24, reported to be 12 times higher than the overall mortality rate from all causes combined (3). Various treatment modalities are employed, encompassing nutritional rehabilitation, individual psychotherapy, family-based therapy, nutritional counseling, and pharmacotherapy (SSRIs) (4–6). Currently, there are no licensed or approved biological treatments for AN, and the effectiveness of psychological interventions and weight restoration treatments varies and typically leads to temporary alleviation of symptoms in around one-third of adolescent patients, with an even lower rate of success in adults (7). Risk factors for AN can be presented in three groups: temperamental/personality, environmental, genetic and physiopathological (8).

The existing literature highlights the presence of brain abnormalities in individuals with AN, particularly in specific areas such as the dorsolateral prefrontal cortex (DLPFC), cingulate cortex, and left middle occipital gyrus (9). Electroencephalographic (EEG) measurements among patients suffering from AN have shown hyperactivity of the right frontal hemisphere (10). Functional magnetic resonance imaging studies reveal diverse patterns of brain activity. Notably, when exposed to food cues, there is reported heightened activity in regions associated with reward, along with increased activation in the right DLPFC (11). These findings suggest an intensified top-down inhibition of reward processing (12). Importantly, the DLPFC is recognized for its pivotal role in cognitive control and self-regulation in dietary contexts (13), therefore, it is reasonable to question whether coupled inhibition of the right hemisphere activity can facilitate interhemispheric balance (14).

Due to the complex etiology of AN and the limited effectiveness of current therapies, coupled with a high mortality rate, there has been a search for new treatment methods. Contemporary research directions in the therapy of AN increasingly focus on neuromodulation and neurosurgery, encompassing neurosurgical ablation, deep brain stimulation, repetitive transcranial magnetic stimulation, and transcranial direct current stimulation (tDCS) (15). In our project, we formulated a hypothesis regarding the effectiveness of tDCS in the treatment of anorexia, measured as a reduction of the severity of eating disorder symptoms. At the time of writing this article, there are also four published research papers (14, 16–18) and two study protocols (19, 20) assessing the effectiveness of such therapy in AN, which encompass diverse approaches and outcomes. As of now, only one double-blind randomized controlled trial (17) has delved into the therapeutic possibilities of tDCS for AN. In this particular study, 43 participants diagnosed with AN were randomly assigned to undergo either active or sham tDCS sessions targeting the left DLPFC over ten 30-minute sessions. While the findings did not reveal significant improvements in AN psychopathology or weight recovery compared to sham tDCS, active tDCS did demonstrate a decrease in the need for excessive control over food intake and an enhancement in body image.

TDCS method serves as a tool for brain stimulation, enabling the stimulation of the cerebral cortex through the use of two or more sponge electrodes with opposing polarities (anode and cathode). These electrodes, soaked in saline, are applied to the scalp (21). This procedure is painless, and considered safe, with minimal to no side effects (22). The stimulator, a battery-powered device, administers a small amount of direct current (typically 0.5–2.5mA), some of which reaches the brain, influencing brain activity based on the applied current’s polarity. tDCS provides two types of stimulation: anodal and cathodal (23). During a tDCS session, a current flows between the electrodes, resulting in non-focal effects. Anodal tDCS depolarizes neurons, increasing their excitability and facilitating firing, whereas cathodal tDCS hyperpolarizes neurons, inhibiting firing below the stimulation site. Typically, the target neurons become less excitable, leading to a decrease in their spontaneous activity (24). According to physiological studies conducted during stimulation, the mechanism of action of tDCS is multidirectional. Studies using positron emission tomography have identified potential mechanisms of action in the structures of the central nervous system of transcranial stimulation: the possibility that tDCS may act through the opioidergic system (increasing the release of endogenous opioids), acting through voltage-dependent sodium channels, dopamine type two (D2) receptors, and through serotonergic (5-HT) receptors. It has also been observed that transcranial stimulation is followed by NMDA receptor activation and a subsequent process of long-term synaptic potentiation (25, 26). An increase in glutamatergic and GABA-ergic activity has also been observed (27).

The study assumed that tDCS treatment would directly or indirectly lead to changes in brain bioelectrical function in the left and right frontal lobe areas. Studies describing the efficacy of tDCS indicate improvements in neurocognitive function, mood, increases in serotonin and dopamine (28, 29). This will create an opportunity to implement more effective and new methods of recovery in the course of AN.

### Objectives

We hypothesized that applying excitatory tDCS could potentially help modify the balance between the two brain hemispheres in children and adolescents with AN. The aim is to diminish their control over eating behaviors and enhance overall improvements in AN psychopathology. Our primary outcome measure involves assessing changes in the Eating Attitudes Test (EAT-26) from baseline to end of stimulation cycle (3 weeks).

A range of secondary outcome measures will be administered to further determine tDCS treatment effects on: 1. anthropometric measurements (in this BMI), 2. brain bioelectric activity, 3. nutritional status, 4. mood, 5. neurocognition (attention, memory, and some aspects of planning, verbal fluency, and another executive function), 6. psychological measurements: dysfunctional metacognitive beliefs, other aspects related to thinking such as reflectivity, impulsivity, obsessive-compulsive symptoms, stress based on subjective feelings related to problems and personal events, 7. selected biological markers related to stress, food intake, inflammation and neurotrophins.

### Trial design

In a single-center randomized, double-blind, placebo-controlled study (RCT), the effect of tDCS (n=25) compared to sham-tDCS (n=25) will be evaluated in patients suffering from AN. The aim is to assess the effectiveness of tDCS in enhancing the clinical outcomes for children and adolescents with AN. We will measure this improvement by evaluating changes in the scores of the EAT-26 (Eating Attitudes Test-26) as our primary outcome. The study was designed according to the guidelines Recommendations for Interventional Trials recommendations (SPIRIT 2013) (30). The duration of intervention was set for three weeks as a main endpoint and with follow-up period 2 weeks after the last tDCS session. The graphical representation of the overall study structure shows **Figure 1**. The RCT was registered in the clinicaltrials.gov database (study ID: NCT05814458).

**Figure 1 f1:**
[figure not shown]
Visual representation of the study protocol.

## Methods: participants, interventions, and outcomes

### Study setting

Recruitment and study activities will be conducted among inpatients at the I Department of Psychiatry, Psychotherapy and Early Intervention at the Medical University of Lublin, Poland.

### Eligibility criteria

A total of 50 inpatients (before accounting for a 20% dropout) with a diagnosis of anorexia nervosa (AN) will be recruited for this study. To be eligible for the trial, subjects must fulfill all of the inclusion criteria and none of the exclusion criteria, as stated below. The following inclusion criteria will be adopted:

Written informed consent to participate in this study before any study-mandated procedure, written by the participant or participant and parent/legal guardian;Female patients aged 13–25 years old;Meet the DSM-5 criteria for AN;Body mass index (BMI)  ≤ 17,5 kg/m2;Participants must not be undergoing psychopharmacotherapy, with the exception of those who have been taking antidepressants for a minimum of 1 month in a stable dose.

The exclusion criteria will be as follows:

No informed consent to participate in the study;Diagnosis of neurological/organic diseases, such as epilepsy;Contraindications to tDCS, ie., pacemakers, metal parts around the head;Any psychiatric comorbidities;Pregnancy or pregnancy planning;Taking medications other than antidepressants or changes in psychopharmacotherapy during the study.

Reasons for the participant to be discontinued from the study:

Withdrawal of informed consent,.Completion of hospitalization before the end of participation in the project.Non-attendance at the study visits and stimulations understood as equal to or greater than 10% of all simulations.Any serious adverse event during the intervention period.

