### Recruitments

The participants of the study will be recruited from consecutively admitted patients for hospital treatment at the University I Department of Psychiatry, Psychotherapy and Early Intervention, Child and Adolescent Psychiatry Unit in Lublin, Poland.

According to the Eating Disorders Therapy Program adopted by our Department, patients with AN have an adaptation period of up to three days. On the fourth day, patients will be informed in detail on the course of the study, all study procedures, potential risks, and the benefits of each intervention. A written document outlining the study will be provided to all participants. This document will include the objectives and rationale of the research, assurances of voluntary participation, the study schedule, potential hazards, the procedures for maintaining the confidentiality of personal data, and the participants’ right to discontinue participation in the study at any moment without the necessity to provide a justification. The next step involves obtaining written informed consent for participation in the study from the participant or participant and parent/legal guardian.

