### Allocation

The patients included in the study will be randomly assigned to one of two subgroups, independently of examined variables, during the entry of the study: Active group - AG (tDCS group, n=25) and Sham group - SG (placebo group, n=25).

Eligible patients will be randomized in equal proportions between the AG and SG arm. A random sequence generator (Urbaniak GC, Plous S. Research Randomizer (Version 4.0) 2013) will be used to randomize active versus sham arms. The allocation to study groups will be performed by a researcher not involved in the stimulation and assessment of patients.

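### The hypothesis and aim name children and adolescents, but eligibility runs from 13 to 25 years: the target population must be reconciled, and age, plausibly prognostic, is worth adjusting for

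*Protocol article*

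**What the plan says.** The protocol article describes its population in several ways.

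- **Objectives:** the hypothesis is that excitatory stimulation "could potentially help modify the balance between the two brain hemispheres in children and adolescents with AN".
- **Trial design:** "The aim is to assess the effectiveness of tDCS in enhancing the clinical outcomes for children and adolescents with AN". The opening sentence of the same section speaks only of patients with AN.
- **Abstract, Background:** the main purpose is given for patients with AN, with no age.
- **Abstract, Methods, and Eligibility criteria:** the range is 13 to 25 years; the criterion reads "Female patients aged 13–25 years old".
- **Measures:** the Beck inventory is assigned to participants over 18, whom the text still calls adolescents. The EAT-26 is described as usable from age 13 and in adults.
- **Study setting:** inpatients of the psychiatry department as a whole.
- **Recruitments:** consecutive admissions to the department's "Child and Adolescent Psychiatry Unit in Lublin, Poland".

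Three other places bear on age. Background and rationale says that existing psychological and weight-restoration treatments lead to "temporary alleviation of symptoms in around one-third of adolescent patients, with an even lower rate of success in adults". Interventions gives treatment as usual to all patients. Allocation says that patients are "randomly assigned to one of two subgroups, independently of examined variables", in equal proportions, 25 per arm. Statistical methods lists ANOVA or rank-based tests and names no age term.

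**The concern.** Objective, eligibility and recruitment source are all stated in this article, and they do not describe the same people. This is not a detail left to a fuller document.

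What is at stake is the wording of the conclusion. If a material number of participants are 18 or over, the primary EAT-26 result is an average over adolescents and young adults, and it does not directly answer a question posed for children and adolescents. If the unit admits very few adults, the result says little about the upper part of the 13 to 25 range.

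A secondary matter is that age is, on the article's own account, plausibly related to how patients fare under the treatment both arms receive. In a trial of 50, the arms may by chance differ noticeably in age.

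**Working it through.** **1. Statements side by side**

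| Place in the article | Population |
|---|---|
| Objectives; Trial design (aim) | children and adolescents |
| Abstract, Background; Trial design (first sentence) | patients with AN, no age |
| Abstract, Methods; Eligibility criteria | females aged 13 to 25 |
| Measures | includes participants over 18 |
| Study setting | the department |
| Recruitments | its child and adolescent unit |

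The range 13 to 25 spans 25 − 13 + 1 = 13 single-year ages, of which 18 to 25 are 25 − 18 + 1 = 8, or 8/13 = 62%. This is a share of eligible ages. It says nothing about the share of patients who will be adults, which the article does not give.

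**2. Is age prognostic?** Existing treatments are said to succeed less often in adults, and both arms receive treatment as usual. Age may therefore be related to EAT-26 change in both arms. No size on the EAT-26 is given, and the statement is not about tDCS.

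**3. Chance imbalance under the stated allocation**

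Inputs: 50 patients, 25 per arm (Allocation). The 50 agrees with the sample size section: 40/(1 − 0.20) = 50. The number of adults K is assumed.

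Let X be the number of adults in the active arm. With an exact 25/25 split and no stratification,

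P(X = x) = C(K, x) · C(50 − K, 25 − x) / C(50, 25),

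and the arms differ by |2X − K| adults. A difference of 5 is 5/25 = 20 percentage points in adult share.

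Worked case, K = 15: the difference is 5 or more when X ≤ 5 or X ≥ 10. The lower tail is 0.07716 + 0.02505 + 0.00531 + 0.00069 + 0.00005 = 0.10826, and doubling gives 0.217.

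| Assumed adults K | P(difference ≥ 5) |
|---|---|
| 5 | 0.050 |
| 6 | 0.022 |
| 10 | 0.074 |
| 14 | 0.114 |
| 15 | 0.217 |
| 16 | 0.128 |
| 20 | 0.148 |
| 24 | 0.156 |
| 25 | 0.258 |
| 26 | 0.156 |

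Parity matters. The difference has the same parity as K, so for even K the smallest difference that counts is 6, and the probability is well below that of the odd neighbours. Over K = 5 to 26 the lowest value is 0.022 (K = 6) and the highest 0.258 (K = 25). Quoting only odd counts would overstate the risk.

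**4. What an imbalance could do.** If adults and adolescents differ by Δ points in mean EAT-26 change under the same treatment, a 20-point difference in adult share shifts the unadjusted group difference by 0.20 × Δ. The article gives no Δ. Purely as an illustration, a Δ as large as the 20-point improvement used in the sample size section would shift the difference by 0.20 × 20 = 4 points.

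**The case against.** The strongest reply is that this is loose wording. The eligible range is stated plainly, twice; the general purpose is given for patients with AN; consent provides for participants signing alone or with a guardian; and people over 18 are called adolescents, which suggests that the term is meant broadly. The primary instrument covers the whole age range. All of this stands, and it is why the mismatch is a matter of reconciling text and not a fault in the trial's validity. It does not remove the mismatch: the aim still names a narrower group than the criteria admit.

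Four stronger readings are tempting, and the documents do not support them.

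- **That ignoring age in allocation produces the population mismatch.** Eligibility and recruitment decide who enrols; allocation cannot change that.
- **That unstratified allocation is an error or biases the result.** Simple 1:1 randomisation is valid, and chance imbalance is already covered by the type I error. Covariate adjustment is also commonly left to an analysis plan, so its absence here is not a fault.
- **That adults will respond less to tDCS, so the effect and power are diluted.** The sentence on adults concerns existing treatments. It supports age as prognostic, not as a modifier of the tDCS effect.
- **That adults are practically unreachable because recruitment is from the child and adolescent unit.** Study setting names the whole department, and no admission figures are given.

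The two possible consequences also cannot both be large. With many adults, age balance and the wording of the aim matter; with very few, the sample fits the aim and it is the 13 to 25 label that lacks support.

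**Conclusion.** The point holds as an inconsistency in the stated target population, of minor to moderate weight. The aim and hypothesis are for children and adolescents, while the eligible population is females aged 13 to 25, with participants over 18 foreseen. As the text stands, a conclusion worded like the aim would not match the sample that the criteria allow. No figure in the article is shown to be wrong.

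Age is plausibly prognostic for the primary outcome. The chance that the arms differ by 5 or more adults lies between about 0.02 and 0.26. That range rests on an assumed 5 to 26 adults among 50 and an exact 25/25 split. Its effect in EAT-26 points cannot be derived from the article. This is a reason to adjust for age, not evidence of bias.

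**What to change.** 1. State one target population in the same words in Objectives, Trial design, Eligibility criteria and Recruitments, and word the conclusions for the ages actually eligible and enrolled. Whether the aim is widened to the eligible range or the two are aligned in another way is for the sponsor to decide. Recruitments and Study setting should also agree on which wards supply patients.
2. If participants aged 18 or over remain eligible, pre-specify age as a covariate in the primary EAT-26 model, and report EAT-26 change by arm within age group (under 18; 18 and over) descriptively, without subgroup claims.
3. If recruitment has not begun, stratifying the randomisation list by the same two age groups is an option. It is not required for validity.

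The cost of step 1 is wording in four sections. Step 2 costs one model term and can be settled before unblinding even if recruitment has started; age is already known from screening. Step 3 would mean two lists instead of one and possibly an incomplete block.

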### Interventions

Patients will be receiving twice a day tDCS (applied current at 2mA) or sham stimulation, for 3 weeks on working days (30 sessions in total). Each stimulation will last 25 minutes and take place at a two-hour interval. The detailed schedule of meetings and measurement methods is presented in **Table 1**.

**Table 1 T1:** Schedule of enrolment, interventions, and assessments.

	Study Period				
	Enrolment	Baseline	Intervention period (tDCS stimulations)	End of the intervention period	Safety Follow-up
Timepoint (day)	-2 to -1	0	1-21 ( ± 1 days)	22 ( ± 1 days)	35 ( ± 7 days)
Visit number	V0	V1		V2	V3
Eligibility screen	X				
Informed consent	X				
Sociodemographic data	X				
Randomization		X			
ASSESSMENTS:					
Weight	X	X	X	X	X
Performing body composition analysis		X		X	X
Psychological		X		X	
Neuropsychological		X		X	
Dietary behaviors and nutrition		X		X	X
Biological	X	X	X	X	
Adverse events	X	X	X	X	X

Participants in the active tDCS group will receive active stimulation to DLPFC via two saline-soaked, 25 cm2 (5 cm x 5 cm) sponges saline-soaked placed over F3 (anode) and F4 (cathode), according to the International 10–20 system. The electrodes will be placed on the patient’s head using a specially designed headband. The patient’s skin should be clean and dry. Each time, it will be checked whether the skin has any wounds, irritations, or other dermatological issues that could affect the safety and comfort of the patient.

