In the sham tDCS condition, an identical protocol was employed. When the system is programmed as Sham, the device will ramp up to the programmed intensity and then back down to a test current of 25 microamps. It will stay at this test current to make sure the contact quality measurement is correct for the remainder of the session and then will ramp up to the programmed intensity and then back down to the test current at the end of the session. The system will ramp up for 30 seconds and back down for 30 seconds at the beginning and the end of each session for Sham stimulation. For Active stimulation, there is an initial ramp up of 30 seconds to the programmed intensity and then at the end of the session, the current ramp down to test current in 30 seconds. The commercially available Soterix Medical Inc. 1x1 tDCS mini-CT LTE device (model 1601-LTE) will be used for stimulation. The first stimulation will take place after obtaining the patient’s written consent, completing questionnaires, performing body composition analysis, EEG and blood tests. The stimulation device will always be triggered by one of the team members. During the stimulation, the patient can move freely and will be encouraged to do activities that additionally stimulate the brain, such as reading, solving crosswords or engaging in conversation. During the school year, simulations will take place during lessons conducted at the hospital. All patients will additionally receive treatment-as-usual, including nutritional rehabilitation, individual and family psychotherapy, psycheducation, and (if necessary) pharmacotherapy.

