### Sample size calculation

The number of studies that examined the effect of tDCS in patients with AN group is relatively small. To calculate the sample size, we analyzed the number of patients in the general population (patients suffering from AN in Poland) (65) and previous trials conducted by other authors (18), which reported improvement in EAT-26 scores. The statistical power was estimated at 80% to detect a difference in means of EAT-26. The baseline EAT-26 points was estimated at 72.7, with a 20-point improvement (18). To account for a dropout rate of 20%, a total of 50 individuals will be included to achieve a target number of 40 participants. Patients will be recruited for the study and randomized into two subgroups. The recruitment target was determined to ensure statistical power, which allows confirmation of the differences in the primary outcomes with an approximately 95% probability of correctly rejecting the null hypothesis. The calculation of sample size was performed using the STATISTICA software (StatSoft) and online sample size calculator (66).

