### Statistical methods

The statistical analysis will be performed by the Statistica package, version 13.0 (StatSoft, TIBCO Software Inc.). Before analysis, the Shapiro-Wilk test will be applied to examine the distribution of examined variables where normality will be assumed if p > 0.05. The chi-square test will be used to calculate differences in the qualitative data at baseline between groups. Depending on data distributions, the between-group comparisons will be performed using the ANOVA or Kruskal-Wallis rank-based nonparametric test for quantitative outcomes. To compare groups between baseline and endpoint assessments and follow-up assessments, repeated measures of ANOVA or aligned rank-transform ANOVA and McNemar’s test will be conducted. All analyses will be performed according to the ICH E9 Statistical Principles for Clinical Trials (67). Bonferroni correction of obtained significance levels will be used to correct for multiple comparisons. The additional characteristics of the participants and dropouts will be performed for an additional assessment of possible non-random differences.

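### Patients are discontinued from the study, not only from stimulation, for events after randomisation, and nothing provides for their primary EAT-26 value at V2

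*Protocol article*

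**What the plan says.** Randomisation takes place at the baseline visit V1, before any stimulation (Study timeline; Table 1). The primary outcome is the change in EAT-26 from V1 to V2, at the end of the three-week stimulation period (Outcomes measures).

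Under Eligibility criteria, a list introduced as "Reasons for the participant to be discontinued from the study" has four entries: withdrawal of consent, "Completion of hospitalization before the end of participation in the project", "Non-attendance at the study visits and stimulations understood as equal to or greater than 10% of all simulations", and any serious adverse event in the intervention period. Treatment is given "for 3 weeks on working days (30 sessions in total").

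The Sample size calculation section allows for 20% dropout: "a total of 50 individuals will be included to achieve a target number of 40 participants". Statistical methods names repeated-measures ANOVA or its aligned rank-transform counterpart, cites ICH E9, and adds: "The additional characteristics of the participants and dropouts will be performed for an additional assessment of possible non-random differences". It names no analysis set.

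On medication, the exclusion criteria include "Taking medications other than antidepressants or changes in psychopharmacotherapy during the study", while the Interventions section gives all patients usual care that includes "psycheducation, and (if necessary) pharmacotherapy".

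**The concern.** The rule ends participation in the study. Non-attendance, discharge and a serious adverse event are treated in the same way as withdrawn consent, although only withdrawn consent prevents further data collection. Each of the three can plausibly be linked to arm or outcome. Discomfort from active current can lead to missed sessions. Recovery or deterioration can bring discharge forward. A serious adverse event may be related to treatment or to clinical course.

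If such patients have no V2 EAT-26, the comparison is between those who stayed, and randomisation no longer protects it. The difference could be biased in either direction. An analysis plan cannot repair this later, because it cannot analyse values that were never collected.

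**Working it through.** **Inputs from the protocol article.** 30 sessions; threshold 10%; 50 randomised 1:1; 20% dropout; target 40; difference 20 EAT-26 points; power 80% (the same section also mentions about 95%). No SD and no alpha are stated.

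**Assumptions.** Two-sided alpha 0.05; sessions missed independently; removal fractions by arm and outcome differences as shown below. The documents give no figures for any of these.

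**1. The plan's own figure.** 40 / (1 − 0.20) = 50. This reproduces.

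**2. The attendance threshold.** 3 weeks × 5 days × 2 = 30 sessions; 0.10 × 30 = 3 sessions, or 1.5 treatment days.

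**3. How often the threshold is met.** P(X ≥ 3) for X ~ Binomial(30, p):

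| Assumed miss rate per session | Patients meeting the rule |
|---|---|
| 2% | 2% |
| 3% | 6% |
| 5% | 19% |
| 10% | 59% |

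At 5%, this rule alone would use nearly all of the 20% dropout allowance. At 2% or 3% it would not.

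**4. The SD implied by the plan.** With 20 per arm, SD = 20 / [(1.960 + 0.842) × √(2/20)] = 22.6 for 80% power. For 95% power it is 20 / [(1.960 + 1.645) × √(2/20)] = 17.5.

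**5. Bias with no true effect.** Let dA and dS be the fractions removed in the active and sham arms. Let m be the number of SDs by which the removed patients' EAT-26 change is worse than their arm mean.

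Bias = [dA/(1 − dA) − dS/(1 − dS)] × m × SD

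With SD 22.6 and 20% lost overall:

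| Removed, active/sham | Bracket | Bias at m = 0.5 | Bias at m = 1.0 | Rejection rate (nominal 5%) |
|---|---|---|---|---|
| 20%/20%, same kind of patient | 0 | 0 | 0 | 5% |
| 24%/16% | 0.316 − 0.190 = 0.125 | 1.4 | 2.8 | 5.4% to 6.8% |
| 28%/12% | 0.389 − 0.136 = 0.253 | 2.9 | 5.7 | 6.8% to 12.5% |

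Equal numbers do not guarantee safety. If both arms lose 20% but for opposite reasons (m = 0.25 to 0.5 in each direction), bias is 2 × 0.25 × m × 22.6 = 2.8 to 5.7 points.

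Bias scales with the SD. At 17.5, the 24%/16% row becomes 1.1 to 2.2 points and the 28%/12% row 2.2 to 4.4.

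**6. Power.** At SD 22.6, 20 per arm gives 80%. If every randomised patient had a V2 value, 25 per arm would give 20 / (22.6 × √(2/25)) = 3.13; 3.13 − 1.96 = 1.17; power about 88%. This is an upper limit, since some patients may withdraw consent.

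**The case against.** The strongest reply is that the article nowhere says assessment stops at discontinuation or that discontinued patients leave the analysis. It cites ICH E9, and analysis sets and missing-data rules are commonly left to an analysis plan that is not shown. The sentence on dropouts describes an additional check and does not say that it is the only handling. Participants are inpatients, with sessions during hospital lessons in the school year, so a 10% miss rate may be far too high. All of this stands. It limits the finding to the stated rule and to data that may never be collected, and it makes the size illustrative.

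A reader might infer more, and the documents do not support it:

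- **That the plan specifies a completer analysis, or breaches ICH E9.** No analysis set is named, so neither can be asserted. What can be said is that analysing all randomised patients at V2 becomes harder if the removed patients are not seen at V2.
- **That a medication change is a stated reason for removal.** It appears among the exclusion criteria and not among the four discontinuation reasons. Removal for it is at most implied.
- **That discharge between V2 and V3 costs the primary outcome.** Participation runs to V3, so the rule is met, but the primary value has already been recorded. Only events before V2 matter for it.
- **That patients with a serious adverse event lose the V3 safety visit.** Discontinuation from the study implies this, but it is not stated. Table 1 lists adverse events at every visit, including V3, and exempts no one.
- **That a fifth of the sample is the most that can be lost.** The 20% is a planning allowance, not a ceiling.

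**Conclusion.** The concern holds in this form. The article states a rule that takes randomised patients out of the study for three kinds of event that may depend on arm or outcome. It makes no provision for their V2 EAT-26 and sizes the trial on 40 of 50 remaining. That the primary comparison would then rest on selected patients is likely, but it is an inference.

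The bias may be nil if both arms lose similar patients. In the unequal-removal scenarios shown, at SD 22.6, it runs from 1.4 to 5.7 points against a 20-point target, which is 7% to 29% of that target. These figures rest on assumed removal fractions, assumed outcome differences of 0.5 to 1 SD, and an SD the protocol does not state. The case for acting rests on the rule itself and on the fact that uncollected V2 values cannot be recovered.

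**What to change.** 1. In Eligibility criteria, separate stopping stimulation from leaving the study. Which events stop stimulation is a clinical decision and is not judged here. Only withdrawal of consent should end data collection.
2. For everyone else, collect the V2 EAT-26, at discharge or as an outpatient if needed, and hold the V3 safety visit. Record the actual assessment date.
3. State that all randomised patients are analysed in their allocated arm, with a likelihood-based model to handle any V2 values still missing.
4. Use the patients who attended more than 90% of sessions only for a supportive analysis.
5. Separately, the clinicians must reconcile the exclusion criterion on medication changes with the pharmacotherapy allowed in usual care. Whichever reading they adopt, the patient stays in the primary analysis.

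The cost is a short amendment and a few paper questionnaires completed outside the ward; the whole dietary set, including the EAT-26, takes up to 30 minutes. The estimate will include partially stimulated patients and so describes assignment to tDCS, not full exposure to it. The number randomised need not change.
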